# Effect of timing of umbilical cord clamping on anaemia at 8 and 12 months and later neurodevelopment in late pre-term and term infants; a facility-based, randomized-controlled trial in Nepal

**DOI:** 10.1186/s12887-016-0576-z

**Published:** 2016-03-10

## Abstract

**Background:**

Delayed cord clamping at birth has shown to benefit neonates with increased placental transfusion leading to higher haemoglobin concentrations, additional iron stores and less anaemia later in infancy, higher red blood cell flow to vital organs and better cardiopulmonary adaptation. As iron deficiency in infants even without anaemia has been associated with impaired development, delayed cord clamping seems to benefit full term infants also in regions with a relatively low prevalence of iron deficiency anaemia. In Nepal, there is a high anaemia prevalence among children between 6 and 17 months (72–78 %). The objective of the proposed study is to evaluate the effects of delayed and early cord clamping on anaemia (and haemoglobin level) at 8 and 12 months, ferritin at 8 and 12 months, bilirubin at 2–3 days, admission to Neonatal Intensive Care Unit (NICU) or special care nursery, and development at 12 and 18–24 months of age.

**Methods/design:**

A randomized, controlled trial comparing delayed and early cord clamping will be implemented at Paropakar Maternity and Women’s Hospital in Kathmandu, Nepal. Pregnant woman of gestational age 34–41 weeks who deliver vaginally will be included in the study. The interventions will consist of delayed clamping of the umbilical cord (≥180 s after delivery) or early clamping of the umbilical cord (≤60 s). At 8 and 12 months of age, infant’s iron status and developmental milestones will be measured.

**Discussion:**

This trial is important to perform because, although strong indications for the beneficial effect of delayed cord clamping on anaemia at 8 to 12 months of age exist, it has not yet been evaluated by a randomized trial in this setting. The proposed study will analyse both outcome as well as safety effects. Additionally, the results may not only contribute to practice in Nepal, but also to the global community, in particular to other low-income countries with a high prevalence of iron deficiency anaemia.

**Trial registration:**

Clinical trial.gov NCT02222805. Registered August 19 2014.

## Background

At the time of birth, the infant is still attached to the placenta via the umbilical cord. The infant is usually separated from the placenta by clamping the cord with two clamps, and cutting between the clamps. This task takes place during the third stage of labour, which is the period of time from the birth of the infant to the delivery of the placenta [1].

Active management of the third stage of labour has been described in a recent World Health Organization (WHO) report as the “cornerstone” of obstetric and midwifery practice during the latter part of the 20th century [2]. Active management has involved the clinician intervening in the process of placental delivery through three interrelated practices: the administration of an uterotonic drug; early cord clamping and cutting; and controlled traction of the umbilical cord.

Early cord clamping has generally been advised to be completed within the first 30 s after birth, regardless of whether cord pulsation has ceased [3]. Due to evidence shown in the last decade, recent guidelines for active management of the third stage of labour no longer recommend immediate cord clamping [4], but changes in practice are still questioned [5] and policies in hospitals are rare [6].

Delayed clamping allows time for a transfer of the foetal blood in the placenta to the infant at the time of birth. This placental transfusion can provide the infant with an additional 40 % more blood volume [7]. The amount of blood transferred to the infant depends on when the cord is clamped and at what level the infant is held prior to clamping [8]. Neonatal benefits associated with this increased placental transfusion include higher haemoglobin concentrations, additional iron stores and less anaemia in early infancy and better cardiopulmonary adaptation [1, 9, 10].

Delayed cord clamping has, however, been linked to an increase in the incidence of jaundice which, in severe cases, could have longer-term effects on the health and development of the infant [1, 11].

Previous studies performed by the principal investigator in a high-income country have shown that delayed cord clamping, compared with early clamping, resulted in a reduced prevalence of neonatal anaemia [12]. Furthermore, delayed cord clamping improved iron status and reduced the prevalence of iron deficiency (ID) in infants at four months of age without demonstrable adverse effects [12–14]. As ID in infants even without anaemia has been associated with impaired development [15, 16], delayed cord clamping seems to benefit full term infants even in regions with a relatively low prevalence of ID anaemia [12].

The improved iron stores at four to six months after delayed cord clamping suggest that ID anaemia could be reduced at eight to twelve months of age, but this could not be shown in a later study by the principal investigators [17], possibly due to small sample size and low frequency of ID anaemia. However, delayed cord clamping was associated with improved fine motor function at 4 years of age [18]. Although ID anaemia is rare (3–9 %) in high-income countries [19], the negative impact on children’s health and development should not be underestimated. No randomized trial has evaluated the effect of delayed versus early cord clamping on infants after six months of age in a low-income country with high prevalence of ID and anaemia. As anaemia is associated with extensive health effects, such as stunting, fatigue and impaired neurodevelopment [20], reducing anaemia in infants is an urgent need globally. In an observational study from Peru, anaemia at eight months of age was evaluated in infants born before and after a hospital policy change from early to delayed cord clamping. The study resulted in a significant reduction of anaemia by 16 % (from 75 to 59 %) as well as a significantly higher level of haemoglobin among infants [21].

In Nepal, there is a high prevalence of anaemia among children aged 6–17 months (72–78 %) [22]. Approximately 50 % of all anaemia among pre-schoolers can be contributed to ID [23]. By performing the planned study in a country with high anaemia prevalence, we aim to evaluate any significant effects on haemoglobin levels and neurodevelopment outcomes after different timing of umbilical cord clamping in this high-risk population.

### Study objective

To evaluate the effects of delayed and early cord clamping on:Anaemia (and haemoglobin level) at 8 and 12 monthsFerritin at 8 and 12 monthsBilirubin at 2–3 daysAdmission to the NICU or special care nurseryDevelopment at 12 and 18–24 months of age.

### Primary outcome

The primary outcome will be pre-specified infant haemoglobin at 8 month of age.

Anaemia will be defined as altitude corrected haemoglobin less than 110 g/L.

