### Sample size

The sample size for the primary outcome at eight months was estimated in order to find a difference of 15 % (70 versus 55 %) in the prevalence of anaemia between the two randomization groups with a power of 80 % and a type I error rate of .05. Using Fisher’s exact-test to analyse outcome data, a group size of 176 would be needed. Taking into account an attrition rate of 35 % we calculated that 270 newborns should be included in each group, i.e. a total of 540.

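### The named primary outcome is haemoglobin at 8 months, but the primary outcome's effect size, power, group size and test are all for anaemia prevalence

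*Protocol article*

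**What the plan says.** Under Primary outcome, the protocol article gives two sentences. The first is "The primary outcome will be pre-specified infant haemoglobin at 8 month of age". The second is "Anaemia will be defined as altitude corrected haemoglobin less than 110 g/L". The second defines a term and does not say that anaemia is the outcome to be compared.

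The Sample size section presents its calculation as the one for the primary outcome at 8 months. Its target is a "difference of 15 % (70 versus 55 %) in the prevalence of anaemia between the two randomization groups". Power is set at 80% and the type I error at 0.05. The section names Fisher's exact test, arrives at 176 per group, and enrols 270 per group (540 in total) to allow for 35% attrition.

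The other sections do not settle which variable is meant:

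- The title names anaemia, and the abstract sets out to "evaluate the effects of delayed and early cord clamping on anaemia (and haemoglobin level) at 8 and 12 months", with the haemoglobin level in brackets. The Study objective section has the same order.
- The closing paragraph of the Background section states the aim in terms of haemoglobin levels.
- Secondary outcomes lists haemoglobin at 12 months, and iron deficiency anaemia at 8 and 12 months. It does not list anaemia as such at 8 months.

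No standard deviation, target mean difference or power is given for haemoglobin.

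**The concern.** Two sections attach the label of primary outcome to different variables. Fisher's exact test compares proportions and cannot be applied to haemoglobin as measured, so the sections cannot both be followed literally. The only outcome with a power statement, anaemia at 8 months, is listed as neither primary nor secondary.

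Two things are at stake. First, a reader who takes the Primary outcome section at its word will attach the 80% to a comparison for which it was not calculated. Second, the article does not fix which comparison decides the trial. The two tests use the same blood samples but need not agree, so a choice made after seeing the data could change the headline result.

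**Working it through.** **Inputs from the article.** Anaemia 70% v 55%; power 80%; type I error 0.05 (sidedness not stated; two-sided reproduces the figure); 1:1 allocation; 176 per group; 35% attrition; 270 per group.

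**Assumptions, not in the article.** For steps 3 to 5, haemoglobin is taken as normal with equal SDs in the two groups. For g/L figures, the SD is taken as 8 to 12 g/L, with 14 g/L as a wider case.

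**1. The article's own figure.** With mean proportion 0.625:

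- Without continuity correction: n = [1.960·√(2·0.625·0.375) + 0.842·√(0.70·0.30 + 0.55·0.45)]² / 0.15² = (1.342 + 0.569)² / 0.0225 ≈ 162.3, so 163.
- With correction: n = (162.3/4)·[1 + √(1 + 4/(162.3·0.15))]² ≈ 175.4, so 176. This matches.
- Exact enumeration of the two-sided Fisher test at 176 per group gives 80.6% power.
- Attrition: 176/0.65 = 270.8, against the stated 270 (270 × 0.65 = 175.5). The difference is negligible.

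The arithmetic is right, and it belongs to anaemia prevalence.

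**2. What 176 per group detects in mean haemoglobin.** At 80% power and two-sided 0.05, the difference is (1.960 + 0.842)·√(2/176) = 0.299 SD. This step needs no anaemia rates.

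| Assumed SD (g/L) | Detectable difference (g/L) | Power for 3 g/L |
|---|---|---|
| 8 | 2.4 | 94% |
| 10 | 3.0 | 80% |
| 12 | 3.6 | 65% |
| 14 | 4.2 | 52% |

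Over differences of 2 to 5 g/L and SDs of 8 to 14 g/L, power runs from about 27% to over 99%. Without an SD and a target difference, the power for haemoglobin is simply not stated.

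**3. The haemoglobin shift equivalent to 70% v 55%.** Under the normal, equal-SD assumption, the shift is z(0.70) − z(0.55) = 0.524 − 0.126 = 0.399 SD (0.3987 unrounded). Power at 176 per group is Φ(0.399·√(176/2) − 1.960) = Φ(1.78) ≈ 96%. About 100 per group would give 80%.

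**4. Type I error if either test may be claimed.** In 200,000 simulated null trials with 176 per group and 70% below the cut-off, the t-test alone rejected in 5.1%, Fisher's test alone in 3.9%, and at least one of them in 7.2%. With 62.5% below the cut-off the last figure was again 7.2%. Two independent tests would give 1 − 0.95² = 9.75%; the inflation is smaller because both tests use the same measurements.

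**5. How often the choice matters.** Under the planned effect and the same assumption, the two tests disagree on significance in about 16.5% of simulated trials, or roughly one in six.

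**The case against.** The best defence is that the Primary outcome section means haemoglobin scored at the 110 g/L cut-off. The definition of anaemia would have little purpose under that heading otherwise. The title and objective put anaemia first, the Sample size section calls anaemia prevalence the primary outcome, and its absence from the secondary list fits its being primary. This is a plausible account of the intent. But the section does not say so, and the article treats haemoglobin and anaemia as separate items in the objective. If this was the intent, the Primary outcome sentence is misworded and still has to change.

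A second defence is that the test for mean haemoglobin may sit in an analysis plan that is not shown. That is fair, and the absence of such a test is not the point. The conflict between the two sections is in the article itself.

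Three stronger readings are tempting, and the document does not support them:

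- A reader might infer that the trial is underpowered. It is not shown to be. The anaemia calculation is correct, and under the normal-shift assumption haemoglobin has more power than anaemia.
- A reader might infer that the investigators plan to test both ways and report whichever succeeds. No section says that. The 7.2% is conditional on such a choice being left open.
- A reader might infer that haemoglobin has to be the primary because a cut-off discards information. That is a design preference. Most of the article is built on anaemia, and naming anaemia as primary removes the conflict equally well.

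**Conclusion.** The inconsistency stands. The outcome named as primary is not the one for which the study was sized, and the outcome that was sized has no place in the outcome lists. The stated 80% is the power for anaemia at 70% v 55% (80.6% by exact calculation), not for haemoglobin.

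The size is moderate: a type I error of about 7.2% instead of 5% if either test could be claimed, with the two tests disagreeing in about one trial in six under the planned effect. Both figures rest on normal haemoglobin with equal SDs, as does the 96% power for the equivalent shift. None of these should be read as a property of the actual data. The contradiction itself needs no assumption. It concerns which analysis is primary, and it calls for no change in the sample size.

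**What to change.** Before unblinded outcome data are seen, name one primary variable and its test, and make the Primary outcome, Secondary outcomes and Sample size sections agree. Either option is acceptable.

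- **(a) Anaemia primary.** State that the primary outcome is anaemia at 8 months (altitude-corrected haemoglobin below 110 g/L), compared by Fisher's exact test. Keep 176, 270 and 540 as they are. List mean haemoglobin at 8 months as secondary. This is the smaller edit.
- **(b) Haemoglobin primary.** State that the primary outcome is altitude-corrected haemoglobin at 8 months as a continuous variable, and name its test. Restate the sample size: 176 evaluable infants per group give 80% power for a difference of 0.30 SD, about 2.4 to 3.6 g/L for an assumed SD of 8 to 12 g/L. If the 96% for the shift equivalent to 70% v 55% is quoted, state the normal, equal-SD assumption with it. List anaemia at 8 months as the key secondary and keep the existing Fisher calculation as its power. Because 0.30 SD is worked back from the group size, add a sentence on why a difference of that size matters; the anaemia calculation remains the reason for keeping 540.

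The cost is a few sentences in three sections and a dated record of the change. No extra infants, visits or measurements are needed.

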### Secondary outcomes

The secondary outcomes will beHaemoglobin at 12 monthsFerritin at 8 and 12 months; definition iron deficiency as ferritin less than 12 μg/LIron deficiency anaemia at 8 and 12 months, defined as both ferritin and haemoglobin below the respective cut offsOther outcomes will be hyperbilirubinemia at discharge, breast-feeding and morbidity during the first six months of life and psychomotor development at 12 months.

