### Follow-up

After delivery, the babies will be cared for according to standard clinical routines, and early breast-feeding will be encouraged. As part of the study, the nurse-midwife will assess the infant at 1 and 6 h, to see whether the baby has been breastfed Infants will stay at the postnatal ward with their mothers for two or three days after delivery, except for those well babies whose mothers prefer to leave the hospital earlier and infants who require admission to the neonatal unit. The SO stationed at the postnatal ward will perform transcutaneous bilirubin measurements when child and mother are discharged from the hospital, as well as 24 and 48 h after delivery if possible. The following information will be collected from maternal healthcare records: background information of the mother’s age and parity, babies’ weight, gestational age and Apgar score.

Monthly, up to 12 months of age, a SO will call the family and ask questions regarding infections, breast-feeding and immunizations of the infant.

At 8 and 12 months of age, infants will be scheduled for a follow-up visit including blood sampling (haemoglobin and ferritin). Venous blood sampling will be performed. Mother’s will be interviewed about the infant’s feeding practice.

At 12 months of age, the Ages & Stages Questionnaire will be used to record infants’ neurodevelopment. Parents will be assisted in answering the Ages & Stages Questionnaire.

If funding is obtained, the Bayley Scales of Infant and Toddler Development, third edition will be used to examine children at 18–24 months of age.

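### Bilirubin is set for 2–3 days in the objective but for discharge in the outcome list, so it is read at differing ages; neonatal-unit admission is an objective with no listed outcome

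*Protocol article*

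**What the plan says.** **Objective.** The abstract lists, among the effects to be evaluated, "bilirubin at 2–3 days, admission to Neonatal Intensive Care Unit (NICU) or special care nursery". The Study objective section repeats both items. The bilirubin item is a level at a stated age.

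**Outcome list.** The Secondary outcomes section ends with a group of other outcomes that includes "hyperbilirubinemia at discharge, breast-feeding and morbidity during the first six months of life". This is a yes/no condition tied to an event, not a level at an age. Admission to neonatal intensive or special care does not appear in the list.

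**Measurement.** The Follow-up section states: "The SO stationed at the postnatal ward will perform transcutaneous bilirubin measurements when child and mother are discharged from the hospital". Further readings at 24 and 48 h are planned only where feasible. The same section expects most infants to remain on the ward until day two or three. It makes an exception of two groups: "except for those well babies whose mothers prefer to leave the hospital earlier and infants who require admission to the neonatal unit".

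**Context.** The Background section names jaundice as a harm linked to delayed clamping. The Ethical considerations section gives hyperbilirubinaemia as its example of a probable adverse effect. The Discussion says that safety effects will be analysed. The Blinding section states that neither mothers nor the delivering nurse-midwives can be blinded.

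**The concern.** The objective and the outcome differ in both measure and time point, and the measurement schedule follows the outcome. Discharge happens after randomisation, and its timing varies by the article's own account. Bilirubin in the first days depends on age, so a status read at discharge does not mean the same thing in an infant who leaves early as in one who stays three days.

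At stake is the comparison of the one adverse effect that the ethics section names. If the readings are scattered in age, a true excess under delayed clamping is harder to see. If infants in the neonatal unit are not read, some cases drop out. If admission to that unit is not a listed outcome, a second stated objective has no defined analysis.

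**Working it through.** **1. The passages side by side**

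| Place | Bilirubin | Neonatal-unit admission |
|---|---|---|
| Abstract; Study objective | level, 2–3 days | named |
| Secondary outcomes | hyperbilirubinaemia, at discharge | absent |
| Follow-up | reading at discharge; 24 and 48 h where feasible | mentioned only as an exception to the ward stay |

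For infants who stay the expected two or three days, discharge and the objective's time point coincide. They separate for the two groups that Follow-up excepts: well babies who leave early and infants admitted to the neonatal unit.

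**2. The plan's own figure.** None is given for bilirubin. The sample size for anaemia supplies the denominator used below.
- Without continuity correction, 70% against 55%, two-sided 0.05, power 80%: [1.960·√(2·0.625·0.375) + 0.842·√(0.21 + 0.2475)]² / 0.15² = 162.3, so 163.
- With continuity correction: (162.3/4)·[1 + √(1 + 4/(162.3·0.15))]² = 175.4, so 176, as stated. Exact Fisher power at 176 per group is 80.6%.
- 176/0.65 = 270.8, so 271 against the stated 270. The figure reproduces.

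**3. Does varying age bias the comparison?** All risks here are assumptions; the article gives none. Let the risk be r_e if read early and r_l if read at 2–3 days, with no true effect, and let f be the share read early in each arm.
- Risk in an arm = f·r_e + (1 − f)·r_l.
- False difference (delayed minus early clamping) = (f_early clamping − f_delayed)·(r_l − r_e).
- The assumed pairs (r_e, r_l) are 2% and 8%, 2% and 12%, and 5% and 15%, so r_l − r_e is 6 or 10 points.

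| Share read early (early clamping / delayed) | False difference |
|---|---|
| 50% / 50% | 0 |
| 50% / 40% | 0.10·(6 to 10) = 0.6 to 1.0 points |
| 50% / 30% | 0.20·(6 to 10) = 1.2 to 2.0 points |

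Swapping the arms reverses the sign. Bias therefore needs a difference between arms in discharge timing, and its direction depends on which arm leaves earlier.

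**4. What varying age does when timing is equal.** Assume a risk ratio of 1.5 at every age and 270 per arm. Power = Φ{[d − 1.960·√(2p̄(1−p̄)/270)] / √[(p₁(1−p₁) + p₂(1−p₂))/270]}.

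| Late / early risk | Share read early | Risks | Difference | Power |
|---|---|---|---|---|
| 8% / 2% | 0 | 8.0% vs 12.0% | 4.0 points | 34% |
| 8% / 2% | 50% | 5.0% vs 7.5% | 2.5 points | 22% |
| 12% / 2% | 0 | 12.0% vs 18.0% | 6.0 points | 50% |
| 12% / 2% | 50% | 7.0% vs 10.5% | 3.5 points | 30% |

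The risk ratio is unchanged, but the absolute difference shrinks and power falls.

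**5. Infants in the neonatal unit.** Assume that 1–5% are admitted, that 30% of those have hyperbilirubinaemia, and that none is read. Missed cases per arm = 270·(0.01 to 0.05)·0.30 = 0.8 to 4.0, about 1 to 4. If admission were 1.5 times as common after delayed clamping, and other infants had a 5% risk, the difference lost would be (0.01 to 0.05)·0.5·(0.30 − 0.05) = 0.1 to 0.6 points.

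**The case against.** The strongest reply is that this is mainly a wording mismatch. The usual stay is two or three days, so a discharge reading is a 2–3 day reading for infants who stay as planned. Readings at 24 and 48 h are also intended. Hyperbilirubinaemia sits among the other outcomes, and an article may leave its cut-off and the analysis model to a fuller document. All of that is fair. It does not remove the contradiction in measure and time point, and early leavers may be the infants who miss the optional 48 h reading.

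Four stronger readings are tempting, and the article does not support them.

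- A reader might infer that the comparison is confounded by age. Randomisation balances age at reading unless clamping, or knowledge of the allocation, alters discharge timing. Unblinded mothers make that possible; nothing in the article shows that it will happen.
- A reader might infer that any bias runs towards no harm. Dilution does work against detecting a difference. Differential timing can act either way: if jaundiced infants in the delayed arm stay longer and are read later, harm is exaggerated.
- A reader might infer that the sickest infants are excluded. The reading is assigned to the postnatal-ward officer, but it is tied to discharge from the hospital, and the stated exception concerns the length of the ward stay. Their measurement is undescribed, not ruled out. Nor would every admitted infant be a case, so missed cases cannot be equated with admissions.
- A reader might call this the main safety outcome. The article gives no outcome that rank.

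**Conclusion.** The point holds in a limited form. Certain from the text: the objective and the listed outcome differ in measure and time point, the only unconditional reading is at an age that varies after randomisation, and neonatal-unit admission is an objective but not a listed outcome. The sure statistical consequence is noise and dilution. Bias is conditional on discharge timing differing by arm and has no predictable sign. Missed cases in the neonatal unit are possible, not established.

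The sizes (power falling from 34% to 22% or from 50% to 30%, a false difference of 0 to 2.0 points, about 1 to 4 missed cases per arm) rest entirely on assumed risks, discharge shares and admission rates. They show scale only, and the contradiction does not depend on them. The primary outcome and the sample size are unaffected. The change is worth making because the article relies on this outcome when it weighs benefit against harm.

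**What to change.** - State one bilirubin outcome, with the same measure and time point, in the abstract, Study objective, Secondary outcomes and Follow-up sections.
- Record age in hours at every reading. Analyse all available readings (24 h, 48 h and discharge) with adjustment for age in hours, or classify hyperbilirubinaemia against an age-in-hours reference at any reading, in place of a single unadjusted discharge status.
- Report age at discharge and number of readings by arm, which shows whether the condition for bias has arisen. Age adjustment makes the available readings comparable; it cannot supply later values for infants who have gone home.
- State that infants in the neonatal unit are counted, with values taken from that unit's records.
- List admission to neonatal intensive or special care as a safety outcome.

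The cost is outcome wording, a time field on the form if there is none already, and chart extraction for a few admitted infants. No extra participants or visits are needed.
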